### Outcome measures

2.5

#### General information collection

2.5.1

General information included age, gender, height, weight, BMI, waist-hip ratio, heart rate and medical history, smoking status, and habitual physical activity level.

#### Primary outcome measures

2.5.2

Functional near-infrared spectroscopy (fNIRS) detection (Part 1): The primary outcome is the cortical hemodynamic response measured by fNIRS, expressed as changes in oxygenated hemoglobin (HbO) and deoxygenated hemoglobin (HbR). Measurements are obtained during the pain-free and high-pain stimulation conditions and compared with the pre-stimulation baseline. The primary comparison is between patients with LMS and healthy controls under the two stimulation conditions. We hypothesize that the cortical hemodynamic responses to pressure stimulation differ between the two groups. The fNIRS system used is a portable 49-channel system manufactured by HuiChuang (Danyang, China), consisting of 20 light sources and 16 detectors. The system uses two wavelengths of 730 and 850 nm, with a sampling rate of 11 Hz and a fixed source-detector separation of 3 cm. The probe array was positioned according to the international 10–10 system, with the D8 optode of the array aligned to the Cz position. Optode positions are recorded for each participant using a three-dimensional digitizing system and registered to Montreal Neurological Institute (MNI) space. The 49 channels cover eight predefined cortical regions: the left and right prefrontal cortex (LPFC and RPFC), left and right supplementary motor area (LSMA and RSMA), left and right primary motor cortex (LSM1 and RSM1), and left and right somatosensory association cortex (LSAC and RSAC) (Figure 2), and recorded data from participants in the static prone position and under different pain stimulations (pain-free range, VAS = 0–3; high pain threshold range, VAS = 7–10). Data preprocessing was performed using Nirspark V1.8.9 software. The preprocessing procedure included channel quality assessment, motion artifact identification and correction, band-pass filtering, conversion of optical density signals to hemoglobin concentration, and baseline correction. Channels with poor signal quality were identified according to the software-based quality control procedure and excluded from further analysis. Motion artifacts were automatically detected and corrected using the built-in motion correction algorithm, with a standard deviation threshold of 6 and amplitude threshold of 0.5. A band-pass filter (0.01–0.1 Hz) was applied to remove physiological noise and low-frequency drift. The modified Beer–Lambert law was used to calculate HbO and HbR concentrations with a differential pathlength factor (DPF) of 6. For the pain-stimulation task in Part 1, task-related hemodynamic responses are analyzed using the general linear model (GLM) implemented in NirSpark. The stimulus function is modeled using the built-in hemodynamic response function (HRF), which is defined in the software by two gamma functions separated by 2 s. The resulting β coefficients of HbO and HbR are used for subsequent analysis. For resting-state and continuous rolling-manipulation data, HbO time series are analyzed using functional connectivity, wavelet amplitude, and graph-theoretical measures. In Part 3, these analyses are used to characterize cortical hemodynamic changes before, during, and after optimal-pressure rolling manipulation.

**Figure 2 fig2:**
[figure not shown]
fNIRS probe placement and channel distribution map. Three-dimensional and two-dimensional representations of fNIRS channel distribution. **(A)** Three-dimensional model showing cortical regions and fNIRS channel distribution. **(B)** Two-dimensional channel distribution model. L, left; R, right; LPFC, left prefrontal cortex; RPFC, right prefrontal cortex; LSMA, Left supplementary motor area; RSMA, right supplementary motor area; LSM1, left primary motor cortex; RSM1, right primary motor cortex; LSAC, left somatosensory association cortex; RSAC, right somatosensory association cortex.

Surface electromyographic signal detection (Part 2): The primary outcomes are the changes in sEMG RMS and MF from before to immediately after each rolling manipulation session. The primary comparison is the difference in these changes among the low-pressure, medium-pressure, and high-pressure conditions within the same participants. We hypothesize that the three pressure levels produce different immediate sEMG responses. The Noraxon Ultium surface electromyography system was used. The subjects took a prone position, and the electrode patches were attached to the marked points of the bilateral lumbar erector spinae and quadratus lumborum. The sEMG signals were recorded before and immediately after each rolling manipulation session with different pressure levels. The time-domain indicator (RMS) and the frequency-domain indicator (MF) were selected as the primary electromyographic outcomes for identifying the optimal pressure level. The RMS reflects the intensity of muscle activation, and the MF reflects muscle fatigue status.

Oswestry Disability Index (ODI) (Part 3): The primary clinical outcome is the Oswestry Disability Index (ODI). The main analysis will compare the change in ODI from baseline to immediately after the 6th intervention between the case intervention group and the case control group. We expect a greater reduction in ODI in the case intervention group. ODI will also be assessed after the 1st and 3rd interventions to describe the course of clinical change. It covered 10 dimensions including pain intensity, activities of daily living, walking, sitting and sleeping, with 0–5 points for each dimension. The total score is converted into a percentage (0–100%), with a higher score indicating more severe dysfunction. Data are collected before intervention and immediately after the 1st, 3rd and 6th interventions to evaluate improvements in patients’lumbar function. If no more than 1 item is missing, the value is replaced by the average score of the completed items; if 2 or more items are missing, the data are regarded as invalid.

#### Secondary outcome measures

2.5.3

Muscle tension detection at marked points of bilateral lumbar erector spinae and quadratus lumborum (Part 1,2,3): A rapid muscle condition measurement system (OE-220, ITO, Japan) is used. The detection positions are the bilateral erector spinae (muscle belly eminence 3 cm beside the 4th lumbar spinous process) and bilateral quadratus lumborum (3 cm beside the 3rd lumbar spinous process at the level between the posterior iliac crest and the 12th rib). The probe is pressed vertically on the marked points until a “beep” is heard, then the reading is taken, repeated 3 times (30s interval) to take the average value, and detected at each time node of pain stimulation intervention, rolling manipulation intervention with different pressure and rolling manipulation intervention with optimal pressure.

Pressure pain threshold detection at marked points of bilateral lumbar regions (Part 1,2,3): A simulated dynamometer (NK-500, ALGOL, Japan) is used, with the detection point at the muscle belly eminence 3 cm beside the 4th lumbar spinous process. The test head is pressurized at a constant rate and supervised by VAS score. When the subject reaches the corresponding pain threshold, he/she reported a pause and the data is recorded, repeated 3 times (30s interval) to take the average value, and detected synchronously with each stage of intervention throughout the process.

Visual Analogue Scale for Pain (VAS) (Part 1,2,3): The pain degree is evaluated by a 10-scale sliding ruler. 0–3 points is the pain-free range/low pressure range, 4–6 points is the moderate intensity pain/medium pressure range, and 7–10 points is the high pain threshold/high pressure range. It is used to supervise the intensity of pain stimulation, define the pressure of rolling manipulation and evaluate the pain relief effect after each stage of intervention, and recorded in real time at each intervention node.

Isokinetic muscle strength testing (Part 2): An isokinetic dynamometer (Biodex System-III, Biodex Medical Systems, Shirley, NY, USA) was used for the test. The participant was seated on the Biodex back testing chair with the trunk upright, the pelvis and thighs secured with straps, and the feet not supported by the footplate to avoid lower limb involvement. The axis of the dynamometer was aligned with the L5 vertebra. The test was performed at angular velocities of 60°/s and 120°/s with five repetitions each, during which the participant performed maximal voluntary lumbar flexion and extension. The measured parameters included peak torque (PT), peak torque to body weight ratio (PT/BW), average power (AP), and flexion/extension ratio (F/E). Isokinetic muscle strength data were collected before and immediately after each intervention session, serving as a secondary biomechanical indicator for the final determination of the optimal pressure level. In addition, sEMG signals from the bilateral erector spinae and quadratus lumborum were recorded simultaneously during the isokinetic test, with electrode placement identical to that described in the surface electromyography section.

### Participant safety

2.6

The inclusion and exclusion criteria are strictly implemented, contraindications are excluded through medical history collection, physical examination and imaging examination, and the informed consent form is signed with the right of voluntary withdrawal clearly stated. During the intervention, the VAS score is used to define the range of pain stimulation and rolling manipulation pressure, and the participants’ feelings are continuously monitored. If discomfort occurs, the intervention is immediately stopped and handled. Tuina operations are performed by professional doctors who have passed standardized training and hold relevant qualification certificates, in accordance with standardized procedures, and manipulation parameters are calibrated by relying on instruments. All detection equipment is regularly maintained, and qualified consumables are selected. An adverse event recording and emergency response mechanism is established. For better prevention and treatment, researchers detected any potential adverse events and recorded them truthfully on the Case Report Form (CRF).

### Quality control

2.7

Random grouping and control design are adopted, the basis for sample size calculation is clarified, a standardized research manual is formulated, and all researchers take up their posts only after passing pre-job training. A supervision group and inspectors are set up, subjects are strictly screened during recruitment, and baseline data between groups are calibrated. For the crossover design in Part 2, the 7-day washout period duration is specifically justified by preliminary observation data to minimize potential carryover effects between successive interventions. Intervention operations are performed by fixed personnel, and manipulations and instruments are regularly calibrated. Detection data follow unified operating specifications, a double entry and review system is adopted, and missing and abnormal data are handled in accordance with regulations. Appropriate methods are selected for statistical analysis with multiple comparison correction, which is completed by professionals with analysis codes retained. Paper and electronic data are managed in a standardized manner throughout the process to ensure research traceability and reliable results.

### Sample size calculation

2.8

Based on the core research objectives and design types of the three parts, this study is overall planned as follows:

The first part is an observational study, with the fNIRS-derived cortical hemodynamic response (HbO/HbR changes) as the primary outcome. Based on repeated measures analysis of variance (effect size *f* = 0.286, α = 0.05, 1−β = 0.8) (30), G*Power 3.1.9.7 calculation showed that 12 cases are needed in each group. Considering a 20% attrition rate, 15 cases are included in both the healthy control group without lumbocrural pain and the lumbar muscle strain case group, with a total of 30 cases.

The second part is a cross-over design. The sample size was estimated based on the median frequency (MF) of the surface electromyographic (sEMG) signals, one of the primary electromyographic outcomes for screening the optimal pressure. Referring to our previous study on rolling manipulation in patients with lumbar muscle strain (13), the within-individual standard deviation of sEMG frequency was 17.09 Hz and the intraclass correlation coefficient was 0.5. Repeated Measures ANOVA combined with Greenhouse–Geisser corrected F test (α = 0.05, 1-β = 0.8) was adopted. PASS 2021 software calculation showed that 17 cases are needed. Considering a 20% attrition rate, 24 patients with lumbar muscle strain are included and randomly divided into 3 group sequences.

The third part took the change in the Oswestry Disability Index (ODI) from baseline to immediately after the 6th intervention as the primary clinical endpoint for the comparison between the case intervention group and the case control group. Based on a two-independent-sample design, in which the expected between-group difference (μ2 − μ1 = 10) and the standard deviation (σ = 9) were derived from a previous study on massage combined with functional exercise for chronic lumbar muscle strain (31), With α = 0.05 and 1 − β = 0.80, the calculation showed that 18 patients were required in each group. Considering a 20% attrition rate, 23 patients with LMS will be enrolled in the case intervention group and 23 in the case control group, resulting in a total of 46 patients with LMS. In addition, 23 healthy controls will be enrolled as a reference group for the fNIRS and biomechanical comparisons. Therefore, Part 3 will include 69 participants in total, comprising 46 patients with LMS and 23 healthy controls.

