### Statistical analysis

2.10

Statistical analyses will be performed using MATLAB R2024b. fNIRS preprocessing and calculation of HbO/HbR concentrations, functional connectivity (FC), wavelet amplitude (WA), and graph-theoretical measures will be performed using NirSpark V1.8.9. Normally distributed continuous variables will be expressed as mean ± standard deviation, non-normally distributed variables as median and interquartile range, and categorical variables as frequencies and percentages. Normality will be assessed using the Shapiro–Wilk test. *p* < 0.05 will be considered statistically significant.

Baseline data: Baseline variables will be analyzed according to variable type, data distribution, and the number of groups using the t test, analysis of variance (ANOVA), Mann–Whitney U test, Kruskal-Wallis test, or chi-square test, as appropriate.

fNIRS data: Task-related fNIRS data will be analyzed using the general linear model (GLM) implemented in NirSpark to obtain channel-wise HbO and HbR β coefficients for subsequent group comparisons. To reduce the risk of false-positive findings arising from multiple comparisons, statistical tests of channel-wise activation will be corrected using the false discovery rate (FDR). Functional connectivity (FC), wavelet amplitude (WA), and graph-theoretical measures calculated in NirSpark will be exported for subsequent statistical analysis using linear mixed-effects models (LMM), with Bonferroni correction applied to multiple comparisons.

Biomechanical and clinical data: Repeatedly measured sEMG, muscle tension, pressure pain threshold (PPT), VAS, and ODI outcomes will be analyzed using repeated-measures ANOVA when the data are normally distributed. For non-normally distributed repeated measurements, generalized estimating equations (GEE) will be used in Parts 1 and 3, whereas the Friedman test will be used for the low-pressure, medium-pressure, and high-pressure conditions in Part 2. Bonferroni correction will be applied where multiple comparisons are required.

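### Part 1 is sized for one F test at alpha 0.05, but the plan compares channel-wise HbO and HbR responses over 49 channels under FDR, so the stated 80% power does not describe the planned analysis

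*Protocol article*

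**What the plan says.** Section 2.8 of the protocol article (Sample size calculation) sizes Part 1 "with the fNIRS-derived cortical hemodynamic response (HbO/HbR changes) as the primary outcome". The method is given as "Based on repeated measures analysis of variance (effect size *f* = 0.286, α = 0.05, 1−β = 0.8"), and the "calculation showed that 12 cases are needed in each group". Then: "Considering a 20% attrition rate, 15 cases are included in both the healthy control group", and the same number in the patient group, 30 in all. The section does not state which ANOVA term was sized, how many repeated measurements were assumed, or their correlation. It makes no allowance for multiple testing.

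Section 2.5.2 (Primary outcome measures) sets the target: "The primary comparison is between patients with LMS and healthy controls under the two stimulation conditions". It hypothesises that the response to pressure differs between the groups. On the measurement it says: "The 49 channels cover eight predefined cortical regions". No channel, region or chromophore is singled out.

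Section 2.10 (Statistical analysis) fits the GLM "to obtain channel-wise HbO and HbR β coefficients for subsequent group comparisons", and adds that "statistical tests of channel-wise activation will be corrected using the false discovery rate (FDR").

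**The concern.** The sizing describes one test at alpha 0.05. The analysis described elsewhere in the same article is a family of up to 49 × 2 = 98 tests per contrast, screened by FDR. A reader will take Part 1 as an 80%-powered comparison of patients and controls, but that figure belongs to a test the plan does not name.

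Two things are at stake. A result in which particular channels or regions fail to survive could be read as adequately powered evidence of no group difference there. And with two chromophores, 49 channels and more than one possible contrast, nothing fixes in advance which result decides the Part 1 hypothesis. Per-channel sensitivity matters because the Discussion gives Part 1 the aim of identifying which cortical regions are involved in pain processing.

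**Working it through.** **Inputs from the article.** f = 0.286, alpha = 0.05, power 0.80, 12 per group (N = 24), 20% attrition, 15 per group (N = 30), 49 channels, two chromophores, FDR.

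**Assumed, because not stated.** Number of measurements m = 2 (the two stimulation conditions) or m = 3 (adding the baseline); correlation rho near 0.5; sphericity; Benjamini–Hochberg at 0.05 as the FDR method.

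**Step 1: reproduce the stated 12 per group.** For a group-by-condition interaction with two groups, the noncentrality is λ = f²·N·m/(1 − rho), with df = (m − 1) and (N − 2)(m − 1).

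- m = 2, rho = 0.55: λ = 0.0818 × 24 × 2/0.45 = 8.7, power 0.81. The smallest even N reaching 0.80 is 24.
- m = 3, rho = 0.45: λ = 0.0818 × 24 × 3/0.55 = 10.7, power 0.81. The smallest N is again 24.
- m = 2, rho = 0.50: N = 28 is needed; power is 0.76 at 24 and 0.86 at 30.
- m = 3, rho = 0.50: N = 22 is needed; power is 0.85 at 24 and 0.93 at 30.

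So 24 in total is an ordinary result for one interaction test, and 12/0.8 = 15 is right.

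**Step 2: the same f for a group main effect.** Here λ = f²·N·m/(1 + (m − 1)·rho), with df = 1 and N − 2. At rho = 0.5:

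| m | λ at N = 24 | power, N = 24 | power, N = 30 | N for 0.80 |
|---|---|---|---|---|
| 2 | 2.6 | 0.34 | 0.42 | 74 |
| 3 | 2.9 | 0.38 | 0.46 | 66 |

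With rho from 0.3 to 0.8 and m = 2 or 3, the total needed runs from 54 to 90. None of this includes FDR.

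**Step 3: direction of the FDR effect.** The Benjamini–Hochberg cut-off is 0.05 × k/K, where K is the number of tests and k the number rejected. Since k ≤ K, it never exceeds 0.05. A channel test with exactly 80% power at 0.05 therefore has less than 80% after FDR, however many channels truly differ.

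**Step 4: size of the FDR effect.** Fix λ so that one test has exactly 80% power at N = 24: λ = 8.59 for df 1, 22 and λ = 10.32 for df 2, 44. Apply Benjamini–Hochberg to independent tests (8,000 simulations). The ranges cover the two df.

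| Truly different | Per-channel power | At least one true channel found |
|---|---|---|
| 1 of 49 | 25–28% | 25–28% |
| 5 of 49 | 34–39% | 78–83% |
| 10 of 49 | 46–49% | 96–98% |
| 24 of 49 | 63–65% | about 100% |
| 49 of 49 | 76% | about 100% |

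If HbO and HbR form one family of 98, per-test power is 19–22% with one true effect, 33–37% with ten, and 76% with all 98.

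**Step 5: if all 30 complete.** With f = 0.286 and rho = 0.5, per-channel interaction power over 49 tests is 33% (m = 2) or 51% (m = 3) if one channel differs, 58% or 77% if ten differ, and 84% or 92% if all differ.

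**The case against.** The strongest reply is that nothing was miscalculated. That stands: 12 per group follows from common inputs, and the article leaves m and the correlation unstated, which the full protocol may supply. A reader who assumes m = 2 and rho = 0.5 might infer that the figure fails to reproduce. That would be a statement about the assumption, not about the plan.

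A reader might also infer that Part 1 will probably end with no or few surviving channels. The documents do not support this, because they do not say how many channels are expected to differ. With ten affected channels, the chance that at least one survives is 96–98% if tests are independent. With a between-channel correlation of 0.3 (m = 2, rho = 0.5) it is about 0.80 at 12 per group and 0.92 at 15. The article does not say which kind of power its 80% means. The loss shown above is in per-channel power, and its size depends on the unknown share of affected channels.

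The group main effect is only one reading. Comparing groups under the two conditions also fits an interaction or a condition-specific contrast. The low figures in Step 2 are therefore conditional.

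Finally, Part 1 is observational, selects no pressure for Part 2 and sizes nothing in Part 3; the article calls its expected evidence preliminary; and FDR control is planned. This lowers the severity but does not remove the mismatch between sections 2.8 and 2.10.

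**Conclusion.** The point holds as a mismatch between sizing and analysis through multiplicity, not as an arithmetic error. It should be fixed, but it does not undermine the trial as a whole. Section 2.8 powers one test; sections 2.5.2 and 2.10 plan up to 98 per contrast and name none as primary.

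That FDR takes a channel test sized at exactly 80% below 80% needs no assumption about how many channels differ. The amount does: from about 25–28% per channel (one of 49 affected) to 76% (all affected) at N = 24, assuming independent tests. Full retention of 30 raises these figures, and they pass 80% only if a large share of channels differ. If the main effect of group is meant, power is about 0.34–0.38 at N = 24 and 0.42–0.46 at N = 30 even as a single test, given m = 2 or 3 and rho = 0.5.

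One ambiguity remains. The FDR sentence refers to activation tests. If it does not cover the group contrasts, the problem becomes uncontrolled false positives: with no true difference, 98 × 0.05 = 4.9 expected per contrast.

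**What to change.** - In 2.5.2 and 2.10, prespecify one primary Part 1 test that matches both the hypothesis and the sizing. An example is HbO in one predefined region or regional summary, with the contrast stated: group by condition, or the group difference in the high-pain condition. The choice matters, because an interaction test alone would miss a group difference of equal size in both conditions.
- Move HbR, the other regions and the channel-wise maps to secondary or exploratory status under FDR. Say whether FDR covers the group contrasts and whether HbO and HbR form one family or two.
- In 2.8, state the effect tested, the number of measurements, the correlation, and the resulting power at 12 and 15 per group. Say that the 80% does not apply to the FDR-corrected channel-wise tests.
- Do not carry over a figure such as 0.86 (interaction, m = 2, rho = 0.5, 15 per group) to a regional summary unless f = 0.286 is shown to apply to it. Averaging affected with unaffected regions could dilute the effect.

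The cost is protocol and analysis-plan wording, with no extra participants or data. The downside is that channel-level localisation and HbR become exploratory.

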Finally, after the completion of the medium-pressure rolling manipulation stimulation operation procedure and detection, the subjects enter a washout period. After the end of the washout period, the subjects receive high-pressure rolling manipulation stimulation, and the operation procedure is the same as that of the low-pressure rolling manipulation stimulation, with the same detection methods and processes for high and low pressure.

The primary outcomes for screening the optimal pressure are the changes in the surface electromyographic (sEMG) indicators of the bilateral lumbar erector spinae, including the time-domain indicator (root mean square, RMS) and the frequency-domain indicator (median frequency, MF). The final determination of the optimal pressure level will be made by combining these primary outcomes with secondary biomechanical indicators, including isokinetic muscle strength, muscle tension, and pressure pain threshold. The outcomes will be analyzed separately. Differences among the low-pressure, medium-pressure, and high-pressure conditions will first be examined for each outcome. For outcomes showing significant differences across pressure levels, regression analysis will be further performed to examine how the outcomes change across different pressure levels (as detailed in Section 3.10). Correlation analyses will also be performed to examine the relationships among the different biomechanical measures. The final pressure will be selected according to the overall pattern of the sEMG and other biomechanical findings within the predefined VAS tolerance range. A favorable change in a single secondary outcome alone will not determine the optimal pressure.

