
**Table 2 tab2:** Study schedule.

Stage	First visit	Pre-intervention	Intervention	Intervention	Post-intervention
Sign informed consent form	X				
Assign group number	X				
Lumbar spine AP & lateral X-ray	X				
Collect basic medical history					
General information	X				
Specialized examination	X				
Clinical DIAGNOSIS	X				
Confirm inclusion criteria	X				
Confirm exclusion criteria	X				
Efficacy observation part 1 trial		Pre-intervention	Intervention	Post-intervention	
Functional near-infrared spectroscopy (fNIRS)		X	X	X	
Muscle tension		X		X	
Pressure pain threshold		X		X	
Visual analogue scale (VAS)			X		
Part 2 trial		Pre-intervention	1st Post-intervention	2nd Post-intervention	3rd Post-intervention
Surface electromyography (sEMG)		X	X	X	X
Isokinetic muscle strength		X	X	X	X
Muscle tension		X	X	X	X
Pressure pain threshold		X	X	X	X
Visual analogue scale (VAS)		X	X	X	X
Part 3 trial		Pre-intervention	1st Intervention	3rd Intervention	6th Intervention
Oswestry disability index (ODI)		X	X	X	X
Functional near-infrared spectroscopy (fNIRS)			Before-during-after	Before-during-after	
Muscle tension		X	X	X	X
Pressure pain threshold		X	X	X	X
Visual analogue scale (VAS)		X	X	X	X
Study evaluation					
Treatment compliance	X				X
Adverse event assessment		X			X
Analysis of dropout reasons					X
Study completion summary					X
CRF statement review					X

To standardize the measurement conditions, all participants in Parts 1, 2, and 3 of the study were asked to maintain their usual daily activity level during the study period and to avoid additional strenuous physical activity. In addition, before each measurement, participants rested in a quiet environment for at least one hour to minimize the acute effect of physical activity on the baseline values.

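### Part 2 is sized for one median-frequency test at alpha 0.05, but its primary outcomes are pre-post changes in both RMS and MF, so the stated 80% power is not shown for the primary outcome set

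*Protocol article*

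**What the plan says.** **Sizing (section 2.8).** "The sample size was estimated based on the median frequency (MF) of the surface electromyographic (sEMG) signals, one of the primary electromyographic outcomes". The inputs are given as "the within-individual standard deviation of sEMG frequency was 17.09 Hz and the intraclass correlation coefficient was 0.5". The method is given as "Repeated Measures ANOVA combined with Greenhouse–Geisser corrected F test (α = 0.05, 1-β = 0.8) was adopted", and "PASS 2021 software calculation showed that 17 cases are needed". Then: "Considering a 20% attrition rate, 24 patients with lumbar muscle strain are included and randomly divided into 3 group sequences". No MF difference between pressure levels is stated, and RMS has no SD or effect.

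**Primary outcomes (section 2.5.2).** "The primary outcomes are the changes in sEMG RMS and MF from before to immediately after each rolling manipulation session". The primary comparison is of these changes among the three pressure levels within participants.

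**Use of the outcomes (section 2.4.2).** The primary sEMG indicators are those of the bilateral erector spinae. Each outcome is analysed on its own, and those that differ significantly across pressures go on to regression. After that, "The final pressure will be selected according to the overall pattern of the sEMG and other biomechanical findings".

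**Multiplicity (section 2.10).** Bonferroni is promised where multiple comparisons call for it. The family it covers is not defined.

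**Schedule (Table 2).** For Part 2 the table has a single pre-intervention column, followed by "1st Post-intervention" and two further post-intervention columns. Sections 2.5.2 and 2.5.3 require sEMG and isokinetic measurements before and after every session.

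**The concern.** The calculation and the primary analysis do not describe the same thing. One MF test at 0.05 was sized; two change variables, analysed separately, are primary. A reader of section 2.8 would take 80% power and 5% error as properties of the Part 2 primary analysis, but they are shown for one MF test only.

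The second issue is scale. An SD and ICC quoted for sEMG frequency read most naturally as describing a single MF value, whereas the primary variable is a difference of two values. Its error variance can be larger or smaller than the one used for sizing, depending on how strongly the pre and post values of one session are correlated.

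This matters because Part 3 uses the pressure that Part 2 selects. A screen with less power than believed, or with looser error control than believed, feeds straight into the efficacy comparison.

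**Working it through.** **1. The plan's own figure.** The 17 cannot be reproduced, because section 2.8 gives no target MF difference. I therefore solved for the effect that gives 80% power at n = 17 and carried it through.

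Model: repeated-measures ANOVA, k = 3 pressures, noncentral F with df1 = 2, df2 = 2(n − 1) and λ = n·Σ(m_i − m̄)²/σ_w² (sphericity assumed). At n = 17 and alpha 0.05, power 0.80 needs λ = 10.60. The implied difference between extreme levels is:

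| Reading of 17.09 Hz | Evenly spaced means | One level differs |
|---|---|---|
| Within-person SD, σ_w = 17.09 | 19.1 Hz | 16.5 Hz |
| Total SD, σ_w = 17.09·√(1 − 0.5) = 12.08 | 13.5 Hz | 11.7 Hz |

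A Greenhouse–Geisser epsilon of 0.75 (my assumption) raises these by about 11% and changes the n = 17 to 24 power figures in step 3 by less than 0.01.

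**2. Attrition.** 17/0.8 = 21.25, so 22, and 24 is the next multiple of 3. This is consistent with the plan. 24 × 0.8 = 19.2, so about 19 completers.

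**3. Two primary outcomes, planned variance.** λ scales as 10.60·n/17. Power of the MF test:

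| Alpha | n = 17 | n = 19 | n = 24 |
|---|---|---|---|
| 0.05 (as sized) | 0.80 | 0.85 | 0.93 |
| 0.025 (Bonferroni over RMS and MF) | 0.70 | 0.76 | 0.88 |

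About 21 completers are needed for 0.80 at alpha 0.025. With no correction, the chance of at least one false positive is 1 − 0.95² = 9.75% for independent tests; RMS and MF come from the same signal, so treat this as an upper illustration. If instead both had to be significant, no alpha correction is needed, but two independent tests at 80% each give 0.8² = 0.64. The power of the RMS test cannot be computed from the article.

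**4. Change score against single value.** Suppose 17.09 Hz and ICC 0.5 describe single MF values with total variance S². The planned within-person error variance is S²(1 − 0.5). A session's pre-post change has variance 2S²(1 − r), where r is the within-session pre-post correlation, which the article does not give. The ratio is 2(1 − r)/0.5 = 4(1 − r), whichever way 17.09 Hz is read in step 1. Dividing λ by this ratio at alpha 0.05:

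| r (assumed) | Variance ratio | n = 17 | n = 19 | n = 24 |
|---|---|---|---|---|
| 0.5 | 2.0 | 0.49 | 0.54 | 0.66 |
| 0.6 | 1.6 | 0.59 | 0.64 | 0.76 |
| 0.7 | 1.2 | 0.72 | 0.77 | 0.87 |
| 0.75 | 1.0 | 0.80 | 0.85 | 0.93 |
| 0.8 | 0.8 | 0.88 | 0.92 | 0.97 |

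Power of 0.80 is reached at r = 0.75 with 17 completers, about 0.72 with 19 and about 0.64 with 24.

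**5. Adjusting for the pre-value.** Simulated power at n = 17 and alpha 0.05, same effect (simulation error about 0.01):

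| r | Raw change | Post-value adjusted for pre-value |
|---|---|---|
| 0.5 | 0.49 | 0.79 |
| 0.6 | 0.60 | 0.80 |
| 0.7 | 0.72 | 0.85 |
| 0.75 | 0.80 | 0.89 |
| 0.85 | 0.96 | 0.97 |

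The adjusted analysis is never below the raw change, and it is close to or above the planned 0.80 throughout.

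**The case against.** The article does not say that 17.09 Hz belongs to a single value. If the earlier study reported it for a pre-post change, step 4 falls away. Even on the single-value reading, r = 0.5 is the floor of the range: it means that pre and post values of one session share nothing beyond the participant. They are taken around a 10-minute manipulation at the same marked points, while sessions are 7 days apart, so a within-session correlation above the between-session ICC is to be expected. A reader might infer from step 4 that Part 2 has only about 49% power. The documents do not support that; above r = 0.75 the change score has more power than planned.

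A reader might also infer that the 5% error rate is lost, and count four tests (two outcomes on two sides, 18.5% if independent and uncorrected) or eight with the quadratus lumborum (34%). That goes too far. Section 2.10 has a Bonferroni clause, the article does not say that the sides are tested separately, and section 2.4.2 confines the primary indicators to the erector spinae. Nor does a null MF result by itself leave Part 3 without a pressure, because selection rests on the overall pattern of findings.

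Enrolling 24 absorbs much of the loss if few drop out, and a full protocol or analysis plan may define the correction family.

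All of this limits the size of the problem. It does not remove the mismatch: if the Bonferroni clause covers RMS and MF, then the calculation at alpha 0.05 is not the one that applies, and RMS remains unsized either way.

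**Conclusion.** The point holds, as a should-fix. Without any assumption about the SD, section 2.8 sizes one MF test, while section 2.5.2 has two primary change outcomes and no success rule. The 80% is shown for that one test only. Under two-outcome Bonferroni at the planned variance, the shortfall at 19 completers is small (0.76 against 0.80) and disappears if all 24 complete (0.88).

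The effect of using the raw change cannot be signed from the article. On the single-value reading, power at 19 completers is 0.54 to 0.92 for r from 0.5 to 0.8. All power figures are conditional on the unstated effect that makes 17 correct. The 5% error rate is best described as not secured, since a correction is promised but its family is open.

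Table 2 contradicts the text on pre-session measurements. Followed literally, it would leave the second and third sessions without the baseline that their change scores need. This is separate from power, and the text makes the intention clear.

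**What to change.** 1. Analyse the post-session value in a mixed model with participant as random effect, pressure, period, that session's pre-value and the participant's mean pre-value, instead of the raw change. Because the session's pre-value is in the model, the estimated pressure differences are the same whether post-value or change is the response, so the outcome can still be reported as a change.
2. Either name MF of the erector spinae, averaged over left and right, as the single primary outcome with RMS as first secondary, or keep both and restate the power at alpha 0.025.
3. In section 2.8, state the MF difference assumed between pressure levels and whether 17.09 Hz is on the single-value or the change scale.
4. Reconcile Table 2 with sections 2.5.2 and 2.5.3, so that the schedule shows a measurement before each Part 2 session.

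The cost is wording and one table correction; the pre-session measurements are already described in the text and no patients are added. The downside is that RMS loses co-primary status or, if both stay, the stated power becomes slightly lower.
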